### Diagnostic accuracy and stage migration

3.1

The secondary endpoint of diagnostic accuracy and stage migration will be performed in a subgroup of patients within Group B where patients will act as their own controls. Hence, the comparison will be made for Na[^18^F]F‐PET/CT versus [^18^F]PSMA‐1007‐PET/CT for diagnosing bone, lymph node and soft tissue metastases. For this purpose, the CECT from the [^18^F]PSMA‐1007‐PET/CT will be used together with the blinded Na[^18^F]F‐PET scan, which will be performed with a ldCT for sparing radiation to participating patients. In the same subgroup, we will determine the rate of stage migration and change of treatment strategy. This will be performed in an MDT‐similar set‐up for research purposes only. In this MDT, clinical information about the patients and the blinded Na[^18^F]F‐PET/CT scans will be used to make a first decision on the treatment strategy, which will subsequently be compared with the clinically decided treatment strategy based on the [^18^F]PSMA‐1007‐PET/CT. Due to potential stage migration in the PSMA group, we expect a change of treatment strategy in a smaller group of patients.

### Statistical analysis plan and sample size determination

3.2

Descriptive statistics will be done according to data type: mean ± standard deviation or median (range) for symmetrically and asymmetrically distributed continuous variables, respectively, as judged visually with histograms including approximating normal curves; and frequencies and percentages for categorical variables.

The analysis of time‐to‐event endpoints (PFS, overall survival) will comprise Cox proportional hazard regressions adjusted for group, risk status (high‐, intermediate‐ and low‐risk PCa) and centre. Graphical displays will comprise Kaplan–Meier plots including risk tables (i.e., patients at risk in each group) and the results of respective log‐rank tests. The analysis of QoL data will comprise the estimation of the group difference in a repeated measurement analysis. Descriptive analyses will be performed, and results presented by proportions. Continuous variables will be compared using a *t* test, and categorical variables using a chi‐squared test. Additionally, regression analysis will be used to identify associations within data. Accuracy assessments of Na[^18^F]F‐PET/CT and [^18^F]PSMA‐1007‐PET/CT will relate to sensitivity, specificity, positive and negative predictive values that will be judged upon the reference standard (Table 3). Exploratory, bivariate testing will consist of unpaired *t* tests, alternatively, Wilcoxon's rank sum test, on continuous variables and chi‐squared test, alternatively, Fisher's exact test, on categorical variables. The level of significance will be 5% (two‐sided). All analyses will be done with STATA/IC 17 (StataCorp, College Station, TX 77845, USA).

A total of 402 patients (201 in each arm) are sufficient to indicate a statistically significant difference in PFS with assumed hazard rates of 0.35 and 0.5 for [^18^F]PSMA‐1007‐PET/CT and conventional staging, respectively, implying a hazard ratio of 0.7. Estimates are based on a study duration of 4 years, consisting of 3 years of accrual time and a minimum follow‐up period of 1 year (two‐sample comparison of survivor functions; exponential test; power: 80%). Accounting for loss to follow‐up of 10%, a total of 448 patients (224 in each arm) will be included in the study.

Regarding the subgroup analysis of diagnostic accuracy of [^18^F]PSMA‐1007‐PET/CT compared with Na[^18^F]F‐PET/CT, we assumed a prevalence of metastases of 30%, sensitivity and specificity of 0.38 and 0.91 for conventional imaging, respectively, and 0.85 and 0.98 for [^18^F]PSMA‐1007‐PET/CT, respectively. Then, a sample size of 128 patients is sufficient to indicate a superior sensitivity for [^18^F]PSMA‐1007‐PET/CT and a non‐inferior specificity for [^18^F]PSMA‐1007‐PET/CT with a non‐inferiority margin of 0.052 (power: 80%). This subgroup analysis will be made and published when the first 128 patients have been recruited in Group B.

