### Eligibility criteria

1.3

The study population comprises men (aged 18 years or older) with newly diagnosed unfavourable intermediate‐ or high‐risk (including locally advanced) PCa^13^ or low‐risk PCa with clinical suspicion of metastases based on other findings (i.e., bone pain or suspicion of lymph node or bone metastasis on the magnetic resonance imaging [MRI] performed before prostate biopsies). The inclusion and exclusion criteria are listed in Table 1. Patients will be recruited from the three urologic departments in the Region of Southern Denmark and referred for imaging prior to treatment in the clinical set‐up. Scans will be performed in three nuclear medicine departments in the region.

**TABLE 1 bco2243-tbl-0001:** Inclusion and exclusion criteria for patient enrolment.

Inclusion criteria, all must be fulfilled	Exclusion criteria, any criterion fulfilled warrants exclusion
Has given informed consent to participate	Consent not given
Can read and understand provided patient information material in Danish	Inability to read and/or understand provided patient information material in Danish
Biopsy verified, newly diagnosed and untreated prostate cancer OR Biopsy performed because of clinically strong suspicion of prostate cancer	Previously given consent to this study withdrawn for any reason
Any, some or all of the following features: PSA ≥ 20 ng/mL OR Gleason score ≥ 4 + 3 OR Tumour stage cT2c or above as determined by digital rectal exploration and/or transrectal ultrasonography Suspicion of metastases as judged clinically, for example, bone pain	Staging by imaging not warranted as judged clinically
Staging by imaging is warranted	Allergy towards Na[^18^F]F, PSMA or other contents in the solutions
	Biopsy performed because of clinically strong suspicion of prostate cancer not confirming the diagnosis
	PSA value above 200 ng/mL

Abbreviations: cT2c, clinical stage T2c; PSA, prostate‐specific antigen; PSMA, prostate‐specific membrane antigen.

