### Enrolment and randomisation

2.1

Patient recruitment will be carried out in a collaborative effort by the regional departments of urology and nuclear medicine. Patients will receive oral and written study information, and acceptance to participate is documented in signed consent forms. Consenting patients will be randomised and allocated into one of the study groups. Randomisation will be performed 1:1 into Groups A and B with stratification according to risk status of high, unfavourable intermediate and low risk with suspected metastases, respectively. The randomisation will be executed in the REDCap database software (https://projectredcap.org/).

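### The Cox model for PFS and OS is valid, but it leaves unused the finer prognostic information in baseline PSA, Gleason score and clinical T stage; prespecifying these covariates is a nearly free gain in power

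*Protocol article*

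**What the plan says.** Section 3.2 of the protocol article sets the time-to-event analysis of PFS and overall survival as "Cox proportional hazard regressions adjusted for group, risk status" (high, intermediate, low) and centre. It names no other baseline covariate for these endpoints. The risk classes match the randomisation in section 2.1, which uses "stratification according to risk status of high, unfavourable intermediate and low risk with suspected metastases".

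Table 1 in section 1.3 lists PSA, Gleason score and clinical T stage among the qualifying features. T stage enters as "Tumour stage cT2c or above as determined by digital rectal exploration and/or transrectal ultrasonography", and one exclusion is a "PSA value above 200 ng/mL".

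The sample size in section 3.2 uses a two-group comparison without covariates ("exponential test; power: 80"%), with yearly hazards of 0.35 and 0.5, a hazard ratio of 0.7, 3 years of accrual and 4 years in total. It arrives at 402 men, raised to 448 for 10% loss. "The level of significance will be 5"%, two-sided.

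**The concern.** Three classes are a coarse summary of prognosis in this population. The third class holds only low-risk men with suspected metastases, so adjustment rests mainly on high against unfavourable intermediate risk. The high class includes locally advanced disease. Among men who qualify on PSA alone, values can run from 20 to 200 ng/mL, a ten-fold range.

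In a Cox model, prognostic information that is left out pulls the estimated hazard ratio towards 1 and lowers power. The scan-based stage cannot fill the gap, because it is determined by the randomised scan. PSA, biopsy Gleason score and T stage by rectal examination or ultrasound do not depend on that scan, so they can be adjusted for. What is at stake is efficiency in the primary comparison, and protection against chance imbalance in these baseline predictors.

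**Working it through.** **1. Reproduce the planned size.** Inputs from section 3.2: hazards 0.5 and 0.35 per year, accrual R = 3, total T = 4, two-sided 5%, power 80%.

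- Event probability with uniform accrual: p = 1 − (e^(−λ(T−R)) − e^(−λT))/(λR). This gives 0.686 (control), 0.564 (PSMA) and 0.6305 at the mean hazard 0.425. The mean over the two arms is 0.625.
- Exponential (Lachin-Foulkes) test: n per arm = [(1.96·√(2·0.425²/0.6305) + 0.8416·√(0.5²/0.686 + 0.35²/0.564))/0.15]² = [(1.484 + 0.642)/0.15]² = 200.8. So 201 per arm and 402 in total, as stated.
- Loss: 201/0.9 = 223.3, so 224 per arm and 448 in total, as stated.
- Expected events: 402 × 0.625 ≈ 251. The Schoenfeld requirement is 4(1.96 + 0.8416)²/(ln 0.7)² ≈ 247. Power at 251 events is 80.7%.

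**2. Simulate the covariate question.** Design: 402 men, about 251 events, 6000 simulated trials per cell (Monte Carlo standard error about 0.5 point). The planned model (group, risk class, centre) is compared with the same model plus one baseline score. The score stands for the information from PSA, Gleason score and T stage that remains within a risk class.

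Assumptions, none given in the document: risk mix 65/30/5%, hazard ratio 1.5 for high risk, no centre effect, and a residual log-hazard SD varied from 0 to 0.7. For scale, men one SD above and one SD below the mean differ in hazard by e^0.6 ≈ 1.8-fold at SD 0.3 and by e^1.0 ≈ 2.7-fold at SD 0.5.

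Two readings of the 0.7 were run. In (A) it is the hazard ratio conditional on the score. In (B) it is the hazard ratio that the planned model itself estimates.

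| Residual SD | (A) planned → fuller | Gain | (B) planned → fuller | Gain |
|---|---|---|---|---|
| 0 | 79.2% → 79.2% | 0 | not run | – |
| 0.2 | 79.0% → 80.2% | 1.2 | 80.8% → 81.6% | 0.8 |
| 0.3 | 77.2% → 79.9% | 2.7 | 82.4% → 85.4% | 3.0 |
| 0.4 | 74.1% → 79.4% | 5.3 | 80.3% → 84.9% | 4.6 |
| 0.5 | 71.4% → 79.9% | 8.5 | 80.4% → 87.2% | 6.8 |
| 0.7 | 65.6% → 80.0% | 14.4 | 81.9% → 93.0% | 11.1 |

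Under (A) at SD 0.5 the planned model estimates a hazard ratio of 0.72 where the conditional value is 0.70. Under (B) the conditional hazard ratio was found numerically, so the planned-model value lies between 0.69 and 0.70; that explains planned-model power slightly above 80%.

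**3. What the table shows.** The gain from the fuller model is similar under both readings. The power of the planned model is not: it falls below 80% under (A) and stays at 80.3% to 82.4% under (B).

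**The case against.** A reader might infer that the stated model costs the trial several points of its planned power. The documents do not support that. The 0.7 in section 3.2 follows from two arm-level hazards and an exponential test without covariates, so reading (B) is at least as close to the plan as (A). Under (B) the 80% is kept, and what is given up is extra power. Nor is 251 expected against 247 required events a warning sign: any trial sized to 80% has a margin of that order.

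A reader might also suspect inflated type I error. In a separate run of 2000 trials at hazard ratio 1.0, the planned model rejected in 5.4% and the fuller model in 5.0%. The standard error is √(0.05 × 0.95/2000) ≈ 0.5 point, so this is noise. Adjusting for the stratification factor and centre is valid.

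The size of the gain is also open to challenge. The risk class presumably already uses much of the PSA, Gleason and T-stage information, and PFS here mixes different progression rules after surgery, radiotherapy and palliative treatment. The document gives no within-class prognostic strength. This stands, and it is why the gain is stated only conditionally.

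Availability is inferred too. Table 1 lists the three features as alternatives, and it admits men biopsied on strong suspicion, so some Gleason scores may arrive after inclusion. The values should still exist before treatment for nearly every man, but a rule for missing ones is needed.

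Finally, an SAP that is not shown might add covariates. But the article states its adjustment set; it does not leave the question open.

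**Conclusion.** The point holds as an efficiency improvement. The planned Cox model is valid and a shortfall from 80% is not shown. Adding the three baseline variables would gain roughly 3 to 8 points of power for PFS if the residual within-class log-hazard SD is 0.3 to 0.5. At 0.2 or less the gain is about 1 point or nothing. At zero residual information both models gave 79.2%, so no loss was seen.

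Confidence is high in the direction and limited in the size. The size rests on the assumed SD and on a single score standing in for several estimated coefficients, though with about 251 events a few extra parameters are affordable. The figures concern PFS only; power for overall survival was not examined.

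**What to change.** In section 3.2, prespecify the Cox model for PFS and overall survival with group, randomisation risk stratum, centre, log baseline PSA, Gleason grade group and clinical T stage. Take all covariates from the pre-treatment assessment, with T stage from rectal examination or ultrasound as in Table 1 and not from the allocated scan. State that there will be no data-driven selection, and give a simple rule for the few missing baseline values. Keep the currently stated model as a sensitivity analysis.

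The cost is a sentence or two and no additional patient or event. The hazard ratio becomes conditional on a few more baseline values, but the stated model is already conditional on risk class and centre. The change should be made before outcomes are compared between the arms, since a later addition would look data-driven.

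### Randomisation is stratified by risk status, but the chi-squared tests of the categorical A-versus-B secondary endpoints, and the log-rank results shown with the Kaplan–Meier plots, do not use the strata: a minor loss of efficiency

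*Protocol article*

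**What the plan says.** Section 2.1 (Enrolment and randomisation) fixes the design. Patients are allocated in equal numbers to the two arms, and the allocation is made "with stratification according to risk status of high, unfavourable intermediate and low risk with suspected metastases". Centre is not named as a stratification factor.

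Section 3.2 (Statistical analysis plan and sample size determination) treats the endpoints differently:

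- **PFS and overall survival.** The analysis "will comprise Cox proportional hazard regressions adjusted for group, risk status (high‐, intermediate‐ and low‐risk PCa) and centre". The randomisation factor is therefore in the model.
- **Kaplan–Meier displays.** The next sentence, on graphical displays, adds risk tables "and the results of respective log‐rank tests". It does not mention strata.
- **Categorical comparisons.** The method is "categorical variables using a chi‐squared test". No strata or covariates are mentioned.
- **Other regression.** "Additionally, regression analysis will be used to identify associations within data". This is not a between-arm comparison of a named endpoint.

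Appendix C lists stage distribution, treatment distribution, frequency of residual disease, QoL and overall survival as the A-versus-B secondary endpoints. QoL has a repeated measurement analysis and overall survival has the Cox model. The other three are categorical, so by elimination they fall under the chi-squared sentence. Section 3.2 does not say whether the Cox or the log-rank result decides the PFS hypothesis.

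**The concern.** Stratified allocation removes between-stratum variation from the comparison of the arms. A test that ignores the strata still counts that variation in its standard error. If the strata predict the outcome, the standard error is too large, the true level falls below 5% and power is lost. For time-to-event data, pooling strata with different hazards also pulls the marginal hazard ratio towards 1.

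At stake is power on three secondary endpoints for which no adjusted analysis is stated. For PFS there is also a question of clarity. Two p-values will be available, one that uses risk status and one that as written does not. They can fall on opposite sides of 5%, and the text names no decider.

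**Working it through.** **1. The plan's own figure.** Inputs from section 3.2: hazards 0.35 and 0.5, 3 years of accrual, at least 1 further year of follow-up, two-sided 5%, 80% power, exponential test. The event probability for hazard h is P(h) = 1 − (e^(−h) − e^(−4h))/(3h).

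- P(0.35) = 0.564, P(0.5) = 0.686 and P(0.425) = 0.631.
- With v(h) = h²/P(h): v(0.35) = 0.2173, v(0.5) = 0.3645 and v(0.425) = 0.2865.
- n per arm = [(1.96·√(2·0.2865) + 0.8416·√(0.2173 + 0.3645))/0.15]² = 200.8, so 201 per arm and 402 in total.
- 201/0.9 = 223.3, so 224 per arm and 448 in total.

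Both stated figures reproduce. The stratification point does not change them.

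**2. Level of the plain chi-squared test under stratified allocation.** Take a binary endpoint with stratum shares w and rates p. The plain test uses the variance p̄(1 − p̄). With arms balanced within strata, the true variance is Σ w·p(1 − p). The true level is 2·[1 − Φ(1.96/√ratio)], where ratio is the true variance divided by the assumed one. Shares and rates below are assumptions.

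| Shares | Rates | p̄(1 − p̄) | Σ w·p(1 − p) | Ratio | True level |
|---|---|---|---|---|---|
| 50/50 | 10%, 50% | 0.210 | 0.170 | 0.810 | 2.9% |
| 50/50 | 10%, 30% | 0.160 | 0.150 | 0.938 | 4.3% |
| 30/65/5 | 80%, 45%, 30% | 0.248 | 0.219 | 0.885 | 3.7% |
| 30/65/5 | 70%, 50%, 40% | 0.247 | 0.238 | 0.962 | 4.6% |

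Simulation agrees: 2.9%, 4.1% to 4.4%, 3.7% and 4.7% respectively.

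**3. Power of the chi-squared test, 224 per arm.** For rates 10%/50% against 21%/61% (an 11-point difference):

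- The true standard error is √[(0.170 + 0.2019)/224] = 0.0407.
- The plain test's null standard error is √(2·0.355·0.645/224) = 0.0452. Power = Φ[(0.11 − 1.96·0.0452)/0.0407] = 70%.
- The stratified null standard error is √(2·0.1890/224) = 0.0411. Power = Φ[(0.11 − 1.96·0.0411)/0.0407] = 77%.

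Simulation gave 70.4% and 76.7%, a loss of about 6 points. Simulated results for the other rows, plain versus Mantel–Haenszel:

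- 10%/30%, 11-point difference: 77% versus 79%.
- 80/45/30%, 10-point difference: 57% versus 61%.
- 70/50/40%, 10-point difference: 57% versus 57%.

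**4. Log-rank shown with the plots.** Simulated with 402 patients, exponential times, follow-up uniform on 1 to 4 years, mean control hazard 0.5 and a within-stratum hazard ratio of 0.7. Entries are power, unstratified versus stratified.

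| Hazard ratio between strata | Two equal strata | Shares 30/65/5 |
|---|---|---|
| 1 | 80% vs 80% | 80% vs 80% |
| 1.5 | not run | 79.5% vs 79.8% |
| 2 | 75% vs 79% | 77% vs 79% |
| 3 | 69% vs 78% | 72% vs 78% |

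In the 30/65/5 column the two smaller-hazard assumptions reduce to one split: the last two strata share the higher hazard. There, the true level of the unstratified test at a 3-fold difference is 3.6%. These figures describe the p-value beside the plot, not the Cox result.

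**5. Disagreement between the two kinds of test.** In a further run under the design effect, the stratified log-rank served as a stand-in for the adjusted Cox result. It was significant when the plain log-rank was not in 3–4% of trials at a 2-fold difference and 6–8% at 3-fold. The reverse occurred in about 1%.

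**The case against.** **The primary analysis already uses risk status.** A reader might infer from the log-rank figures that the PFS or overall survival conclusion loses power. The document does not support that. The Cox models include risk status and centre, and the log-rank results appear only among the graphical displays. A log-rank p-value on an unadjusted Kaplan–Meier plot is common practice. This objection stands. The loss reaches the PFS conclusion only if the figure's p-value is taken as decisive, and the text neither says so nor excludes it.

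**Silence is not a statement.** The article says neither stratified nor unstratified for the log-rank, and a fuller analysis plan may specify it. That is fair, so the log-rank part is limited to the text as written. The chi-squared test is different, because it is the method the document names.

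**The planned hazard ratio may be an overall one.** The sample size rests on a two-group exponential test. If 0.7 is the overall rather than the within-stratum hazard ratio, unstratified log-rank power stays at roughly 78–79% even with 3- to 4-fold strata, and stratifying is a gain beyond the planned 80%. This also stands: the table in the working does not show that the plan misses its own target.

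**The binary illustration fits the endpoints loosely.** Residual disease is defined only after prostatectomy, and the Discussion expects treatment proportions not to balance between arms. That endpoint therefore has fewer than 224 per arm, and stratum balance is not guaranteed among operated patients. Stage has six categories, and Appendix E shows mock cells of 0% and 4%. Both points stand and shape the remedy.

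**Type I error.** A reader might also take the mismatch as inflating false positives or biasing the comparison. It does neither; the error is in the conservative direction.

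**Conclusion.** The point holds as a minor efficiency issue. It is clearest for stage distribution, treatment distribution and residual disease, where the named test ignores the randomisation strata and no adjusted A-versus-B comparison is stated.

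The size depends on how strongly risk status predicts each endpoint. In the scenarios tried, the chi-squared loss runs from about zero to about 6 points, and the true level from 4.7% down to 2.9%. All stratum shares and rates are assumed, and the largest figure comes from two equal strata at 10% and 50%. For residual disease and six-category stage, these figures indicate direction only.

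For PFS and overall survival, nothing is lost if the adjusted Cox model decides. What remains there is an unnamed deciding analysis and a displayed log-rank that, as written, leaves out the strata.

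**What to change.** In section 3.2:

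1. Compare stage distribution, treatment distribution and residual disease between arms with a generalised Cochran–Mantel–Haenszel test stratified by randomisation risk status, or with a regression adjusted for it. Collapse sparse stage categories by a rule set in advance. For residual disease, state the analysed population; if it is operated patients only, a risk-adjusted comparison improves precision but does not restore the balance given by randomisation.
2. Stratify the log-rank test shown with the Kaplan–Meier plots by risk status.
3. State that the group effect from the adjusted Cox model decides the PFS hypothesis.

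The cost is a few sentences, slightly more analysis work and a decision on how to collapse stage. The strata are needed for randomisation in REDCap, so no new data are required. If the low-risk stratum proves small, it will carry little weight. The sample size does not change.

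### The only rule stated for comparing categorical variables is an independent-sample test, but the Na[18F]F versus PSMA comparison in Group B is within-patient and includes a non-inferiority margin

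*Protocol article*

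**What the plan says.** Section 3.1 places diagnostic accuracy and stage migration in a part of Group B "where patients will act as their own controls". Each of these patients has both PET scans, and the contrast-enhanced CT from the PSMA examination is read with the blinded Na[18F]F scan as well. For stage and treatment, "we will determine the rate of stage migration and change of treatment strategy". The treatment decision based on the Na[18F]F scan is made first, "which will subsequently be compared with the clinically decided treatment strategy based on the" PSMA scan in the same patient.

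Section 3.2 gives the methods. The general rule for comparing variables is a t test for continuous ones "and categorical variables using a chi‐squared test". A later sentence begins "Exploratory, bivariate testing will consist of unpaired" t tests, with the rank sum test as alternative, and goes on to "chi‐squared test, alternatively, Fisher's exact test, on categorical variables". The sentence on accuracy lists sensitivity, specificity and predictive values, judged against Table 3, and names no test. The significance level is 5% two-sided.

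The same section sizes the subgroup at 128. It assumes 30% prevalence, sensitivity 0.38 and specificity 0.91 for conventional imaging, and 0.85 and 0.98 for PSMA. The aims are superior sensitivity and non-inferior specificity with margin 0.052 at 80% power.

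**The concern.** Chi-squared and Fisher's exact tests compare proportions from independent groups of patients. In the Group B subgroup the two proportions come from the same patients. The general rule is written without exception, so read literally it also covers the paired comparison. No other method for a categorical comparison is stated. The section does allow for repeated observations on one patient in its quality-of-life analysis, but not here.

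Two things are at stake. First, a test that ignores pairing has the wrong reference variance, so its error rate is not the nominal one and the precision gained by scanning patients twice is lost. Second, one of the two planned conclusions is non-inferiority against a margin. The usual chi-squared test addresses the hypothesis of no difference and says nothing about a margin. The subgroup results are to be analysed and published once the first 128 patients are in Group B, so the method needs to be settled before then.

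**Working it through.** **Inputs from section 3.2.** N = 128 and prevalence 0.30, hence 128 × 0.30 = 38.4 diseased and 128 × 0.70 = 89.6 non-diseased. Sensitivities are 0.38 and 0.85, specificities 0.91 and 0.98, margin 0.052, power 80%. The within-patient correlation is not given, so it is assumed and varied.

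**1. The plan's own 128.** An independent two-sample non-inferiority formula, with specificity 0.98 in both tests and one-sided 5%, gives (1.645 + 0.842)² × 2 × 0.98 × 0.02 / 0.052² = 89.6, rounded up to 90 non-diseased; 90 / 0.7 = 128.6. This agrees with 128, but it needs 0.98 for conventional imaging (0.91 is stated) and a one-sided 5% level (two-sided is stated). It is also identical to a paired formula with zero correlation. With 0.91 versus 0.98, the independent formula gives 77 (one-sided 2.5%) or 61 (one-sided 5%).

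**2. Error rate of chi-squared on paired data.** If both tests have the same true rate and within-patient correlation ρ, the variance of the difference is (1 − ρ) times what the independent-sample test assumes. In large samples the true two-sided error is therefore 2 × [1 − Φ(1.96 / √(1 − ρ))].

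- ρ = 0: 5%.
- ρ = 0.25: 1.96 / 0.866 = 2.26, error 2.4%.
- ρ = 0.50: 1.96 / 0.707 = 2.77, error 0.6%.
- ρ = 0.75: 1.96 / 0.5 = 3.92, error below 0.02%.

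With equal rates the maximum ρ is 1, so these are a quarter, half and three quarters of maximum dependence. Simulation (200,000 paired tables per scenario) agrees, and gives about 7% under mild negative dependence. Asymptotic McNemar stays between 4.3% and 5.3%.

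**3. Standard error of the specificity difference at the stated rates.**

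- Unpaired: √[(0.91 × 0.09 + 0.98 × 0.02) / 89.6] = √(0.1015 / 89.6) = 0.0337.
- Covariance at ρ = 0.3: 0.3 × √(0.0819 × 0.0196) = 0.0120.
- Paired: √[(0.1015 − 2 × 0.0120) / 89.6] = 0.0294.
- Ratio: 0.0337 / 0.0294 = 1.14.

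The largest feasible covariance is 0.91 − 0.91 × 0.98 = 0.0182, that is ρ = 0.0182 / 0.0401 = 0.45. Across the range the unpaired standard error is too wide by 0% (ρ = 0), 10% (half of maximum, paired 0.0305), 14% (ρ = 0.3) and 25% (maximum, paired 0.0270).

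**4. Does a paired analysis change what 128 can deliver?** The range runs over all feasible discordance.

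| Aim | Discordance | Power at N = 128 | N needed for 80% |
|---|---|---|---|
| Sensitivity, McNemar, two-sided 5% | 0.47 / 0.584 / 0.77 | 99.9% / 99.1% / 94.6% | 47 / 61 / 83 |
| Specificity, paired non-inferiority, one-sided 2.5% | 0.07 / 0.106 / 0.11 | 99.5% / 95.2% / 94.5% | 49 / 76 / 79 |

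The middle value in each row is conditional independence, for example 0.38 × 0.15 + 0.85 × 0.62 = 0.584. In all cases 128 is enough.

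**The case against.** The best defence is that the article never assigns an independent-sample test to the paired comparison. Accuracy has its own sentence, which names no test. Fisher's exact, the rank sum test and the explicitly unpaired t test stand only under exploratory testing. The general chi-squared sentence is correct for the Group A versus Group B endpoints (stage, treatment, residual disease). A condensed article may leave the choice of paired test to a full analysis plan that is not shown. This limits the weight of the point. It does not remove it, because the rule as printed has no exception and is the only one that a reader can apply to the subgroup.

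The document does not support four stronger readings.

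- A reader might infer that confidence intervals will be wrong. No interval method is stated; the standard errors above show only what an unpaired interval would cost.
- A reader might infer that real stage migration or treatment change could be declared non-significant. Section 3.1 plans to determine rates, which are one-sample proportions. It states no significance test between the two scans for either.
- A reader might infer that 128 was calculated as if the samples were independent. The agreement in step 1 is a back-calculation with two inputs that differ from the text, and the article does not name its formula.
- A reader might expect pairing always to gain power. For a test of any difference in specificity (0.91 versus 0.98, 90 non-diseased, half of maximum dependence), power is 54% with chi-squared, 66% with asymptotic McNemar and 50% with exact McNemar.

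**Conclusion.** The mismatch between sections 3.1 and 3.2 is real and worth correcting, but its consequences are moderate. Followed as written, the stated rule gives invalid p-values for the within-patient comparison unless dependence is zero. The direction is conservative provided that dependence is positive. That is an assumption, though a reasonable one because both readings share a CT. The clearest gap is that no stated test can support the non-inferiority conclusion on specificity. For sensitivity, both chi-squared and McNemar exceed 99% power at the stated rates with positive dependence, so that conclusion would hardly change. The size of the excess in the specificity standard error rests on the assumed correlation, which the article does not give.

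**What to change.** In section 3.2, or in the full analysis plan before the 128-patient analysis:

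- State that chi-squared, Fisher's exact and unpaired tests apply to Group A versus Group B only.
- For Na[18F]F versus PSMA within Group B, use McNemar's test for superiority of sensitivity, and say whether it is the exact or the asymptotic version.
- For specificity, use a confidence interval for a paired difference (score type) compared with the 0.052 margin, with its level stated.
- Report stage-migration and treatment-change rates with one-sample confidence intervals. Use McNemar (two categories) or Stuart–Maxwell/Bowker (the stage table) only if a directional shift is to be tested.

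The cost is a few lines of text. Sample size, recruitment and procedures stay as they are.
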